## Methods

2

### Study design

2.1

The present study combines a multicentric, double-blind feasibility RCT with two parallel study arms to evaluate feasibility (Objective 1) and explore preliminary effectiveness (Objective 2) with an experimental neurophysiological proof-of-concept study assessing the neurophysiological effects of Alc-IT (Objective 3). Following the relevant CONSORT guidelines (Eldridge et al., 2016) and similar to recent feasibility RCTs in this domain (Manning et al., 2021; Manning et al., 2020; Prior et al., 2021), the present study will collect indicators for feasibility from patients and care providers (Objective 1), while also examining preliminary effectiveness by comparing drinking behavior change from pre- to post-treatment between the Alc-IT group and an active control group (Objective 2). The EEG sub-study is designed as an experimental neurophysiological study, which will assess neurophysiological effects of Alc-IT to delineate its working mechanisms as well as moderators of treatment effects on a neuronal level (Objective 3).

### Study population

2.2

A total of up to 210 adolescents and young adults with AUD currently undergoing outpatient treatment or (online) counselling in one of 5 specialized treatment settings within Switzerland will be recruited.

#### Eligibility criteria

2.2.1

Participants fulfilling all of the following inclusion criteria are eligible for the study; (1) age 14–27 years, (2) currently undergoing outpatient treatment or online counselling in one of participating specialized treatment centers, (3) a score of ≥ 8 in the Alcohol Use Disorder Identification Test (AUDIT; Babor et al., 2001), (4) a score of ≥ 2 in the Alcohol Use Disorder Screening (AUD-S; Knight et al., 2002), (5) sufficient German language skills, (6) owner of a smartphone with internet access. The presence of any one of the following exclusion criteria will lead to exclusion of the participant: (1) Other severe substance use (except nicotine and cannabis) determined by values ≥ 25 in the Drug Use Disorder Identification Test (DUDIT; Berman et al., 2005), (2) current medical conditions excluding participation.

Additional exclusion criteria for EEG sub-study are as follows: (1) Current medication affecting EEG (e.g., benzodiazepines), (2) other severe substance use (except nicotine) determined by values ≥ 25 in the DUDIT, (3) history of epilepsy, (4) cochlea implant.

### Recruitment and screening

2.3

Participants will be recruited in collaboration with five specialized outpatient treatment or online counselling settings. Initial contact will be made by treatment providers or study team members. Individuals expressing interest will receive written and verbal information about the study. If they agree to participate, written informed consent will be obtained. In case of minors, informed consent of parents or legal representatives will also be obtained. After obtaining informed consent, participants will undergo formal screening to determine their eligibility.

Due to additional time-consuming measurements in the EEG sub-study, a two-leveled recruitment process will be implemented: Participants in the main study will be asked if they are interested in participating in additional EEG measurements during the pre- (T2) and post-training assessment (T3; see Figure 1). If so, additional information for the EEG sub-study will be provided. If the participant agrees to participate, additional written informed consent and screening will be obtained from the participants.

**Figure 1 fig1:**
[figure not shown]
Study design and participant flow. T0 to T5 denote different assessment time points, ranging from screening to 3-month follow-up. Note that for the EEG sub-study, additional EEG measurements will be conducted at pre- (T2) and post-training (T3) in a subsample. See Table 1 for an overview of questionnaires and measures gathered at each assessment. AUDIT = Alcohol Use Disorder Identification Test (Babor et al., 2001), AUD-S = Alcohol Use Disorder Screening (Knight et al., 2002), DUDIT = Drug Use Disorder Identification Test (Berman et al., 2005), TLFB = Timeline Follow-Back (Sobell and Sobell, 1992; Sobell and Sobell, 1995), EEG = electroencephalography, Alc-IT = mobile alcohol-specific inhibition training, Con-IT = mobile non-specific inhibition training.

**Table 1 tab1:** Schedule of enrolment, treatment and assessments according to SPIRIT.

Timepoint	Study period								
	Enrolment		Allocation	Post-allocation			Follow-up		
	T0	T1		T2	IT	T3	T4	IT	T5
Enrolment									
Eligibility screen	X								
Study information	X								
Informed consent	X		X						
Randomization									
Interventions									
Alcohol-specific inhibition training (Alc-IT)					X			X	
Control training (Con-IT)					X			X	
Assessments									
Feasibility Recruitment and completion rates, treatment adherence, and adverse events		X		X	X	X	X		X
Drinking behavior TLFB		X					X		X
Usability, user experience, and acceptability SUS, UEQ, Web-CLIC						X			
Open-text questions						X			X
Diagnostics AUDIT,	X						X		X
AUD-S,	X								
DUDIT	X						X		
AUD, psychopathology, and related measures HDL, Drinking goals		X					X		X
BSCL, DERS		X							
WHOQOL-BREF, SOCRATES, OCDS-G		X					X		
Craving, Motivation		X		X		X	X		X
Baseline measures (Socio-)demographics, I-8, ASRS-V1.1		X							
Neurophysiological effects (EEG sub-study) EEG assessment including BIS/BAS, GNG task				X		X			

ASRS-V1.1: adult ADHD self-report scale, including impulsivity subscale, AUDIT: Alcohol use disorders identification test; BIS/BAS: behavioral inhibition system/behavioral approach system scale; BSCL: brief symptom check list; Craving: likert scales measuring craving; DERS: difficulties in emotion regulation scale; GNG task: Go-NoGo task; HDL: health and daily living form, including measures on heavy drinking and days abstinent; I-8: scale for impulsive behavior; Motivation: visual analogue scale to measure motivation; OCDS-G: Obsessive compulsive drinking scale – German; SOCRATES: stages of change readiness and treatment eagerness scale; SUS: system usability scale; TLFB: timeline follow-back, from which measures of heavy drinking days and days abstinent will be derived; UEQ: user experience questionnaire; open-text questions concerning drawbacks and strength of the app, technical problems encountered, suggestions for amelioration, intention to continue using the app, place of using the app; Web-CLIC: facets of website content questionnaire; WHOQOL-BREF: WHO quality of life scale.

### Randomization and blinding

2.4

After the baseline assessment (T1), participants are allocated to one of two study groups (see Figure 1) by a secure web-based system hosted at the University of Bern using a randomization list stratified by age, gender, and treatment center.

Participants, clinical staff and members of the study team will be blinded. An exception is made for those members of the study team, who administrate the app. However, they do not have direct contact with the patients. To ensure blinding, all study personnel, especially outcome assessors, will be instructed not to engage in discussions with patients concerning their assumptions regarding the allocated training version.

### Sample size determination

2.5

Note that the present feasibility RCT is not designed to statistically test hypotheses regarding effectiveness outcomes but will rather yield preliminary findings into the effect size to be expected in a future full scale RCT (Eldridge et al., 2016; Thabane et al., 2016; Thabane and Lancaster, 2019). Sample size determination followed recommendations for sample sizes in pilot and feasibility trials that allow for an acceptable estimation of future effect sizes. These recommendations suggest that for small effects, sample sizes ranging from 25 to 75 per study arm are sufficient (Whitehead et al., 2016). Given the recruitment estimation in the five treatment centers^1^, we expect to collect complete data for drinking behavior outcome from 90 patients, which aligns with these recommendations.

For the EEG sub-study, a power analysis was conducted. Using the observed neurophysiological effect size of 0.255 in our prior study (Tschuemperlin et al., 2019) as an estimate and adapting power analyses performed with R to randomization statistics (Manly, 2007), the relevant effects can be detected with a power of 0.8 and alpha-level of 0.05 starting from a sample size of 55. Therefore, complete data will be collected from 60 patients in the EEG sub-study.

### Procedure

2.6

After providing written informed consent (Figure 1), participants will be invited to download the newly developed MINTRA app, which provides access to assessments and training and displays individual study timeline and training progress (see Figure 2). Participants undergo screening assessment during week 1 (T0), followed by the baseline assessment (T1), comprising self-report questionnaires and a structured telephone interview. Participants are then randomized to one of the two study groups (Alc-IT or Con-IT). Before the core training phase, a pre-training assessment with questionnaires (T2) is conducted. Over the subsequent two weeks, participants complete six short training sessions of their allocated version before a post-training assessment (T3, identical to T2) is conducted. One month later, the first follow-up assessment (T4) takes place after which participants complete six additional training sessions over a two-week period. The last follow-up assessment (T5) occurs two months after T4. Both follow-up assessments (T4 and T5) include questionnaires and telephone interviews. All questionnaires are completed within the app. In the EEG sub-study, pre- (T2) and post-training (T3) assessments will take place in the EEG lab and will be complemented by 64-channel EEG measurements during rest and during a Go/NoGo task (see 2.10). To promote adherence throughout the study, participants receive automated push notifications via the app as initial reminders. If adherence issues persist, participants are subsequently contacted by phone based on a structured contact scheme to encourage participation.

**Figure 2 fig2:**
[figure not shown]
Illustrative screenshots of the MINTRA app interface in German. The app serves as the central platform for assessments, access to training, and progress tracking throughout the study. **(a)** Home screen welcoming the participant and providing navigation instructions. **(b)** Overview of the personal study timeline indicating completed steps and access to the current study timepoint. **(c)** Training start screen informing participants about session duration and instructions.

### Study intervention and comparator

2.7

Both training conditions are implemented as modified Go/NoGo tasks (Stein et al., 2023; Tschuemperlin et al., 2019), with identical visual layout, stimuli, and Go/NoGo cues. The conditions only differ in their respective probabilities of pairings between picture-type and NoGo-cues. Each session comprises 320 trials and takes about 10 to 15 min to complete. On each trial, a picture (alcohol-related or neutral) is presented in combination with a letter cue (“p” or “f”) appearing right outside one of the corners of the picture. The assignment of letters as Go or NoGo cues is counter-balanced across participants (see Figure 3). Neutral pictures are identical for all participants, whereas alcohol pictures are individually matched to each participant’s drink of choice (beer, wine, or spirits). Stimuli remain on screen for 1,500 ms. Participants are instructed to tap the screen as quickly and accurately as possible when a Go cue is shown and to withhold their response when a NoGo cue is shown. Visual feedback follows 500 ms after the (non)response (green circle = correct; red crossed-out circle = incorrect). Pictures and cue locations are randomized within each session.

In the Alc-IT condition, alcohol-related pictures are solely combined with NoGo cues and the Go/NoGo ratio is 75/25.In the Con-IT condition, both picture types (alcohol-related, neutral) are paired with Go and NoGo cues equally often.

**Figure 3 fig3:**
[figure not shown]
Illustrative screenshots of the study intervention. **(a)** A neutral picture with the letter cue “f” as a Go cue requiring a touch response **(b)** Correct response feedback (green circle) following a Go trial. **(c)** Alcohol-related picture (in this example: drink of choice = spirits) paired with the letter cue “p” as a NoGo cue where participants must withhold their response. **(d)** Incorrect response feedback: red crossed-out circle shown when a response was made following a NoGo trial.

### Risk management

2.8

Patients will be exposed to pictures of alcoholic beverages during the training. Even though this is not unusual, as patients tend to encounter (pictures of) alcohol in their everyday life as well, this might induce craving. Therefore, patients are asked to rate individual craving and stress levels after each session. In case of high values, emergency numbers will be made available in the Alc-IT app. It is important to note that in a prior RCT including the present alcohol-specific inhibition training with pictures of alcohol, no adverse events relating to the training were found (Stein et al., 2023; Tschuemperlin et al., 2019).

### Outcome measures

2.9

#### Demographics

2.9.1

Relevant demographics (e.g., age, gender, education) as well as relevant information about past AUD treatment or other mental health problems will be assessed.

#### Screening

2.9.2

To evaluate eligibility, the following screening questionnaires will be used: The AUDIT (Babor et al., 2001), a screening questionnaire from the World Health Organization consists of 10 items about recent alcohol use, AUD symptoms, and alcohol-related problems. Self- rated symptoms of AUD will be assessed with the AUD-S (Knight et al., 2002), adapted to DSM-5 criteria as in Tschuemperlin et al. (2019). The DUDIT (Berman et al., 2005) is an 11-item self-administered screening instrument for drug-related problems, giving information on the level of drug intake.

#### Primary outcome

2.9.3

Following the CONSORT guidelines’ extensions for pilot and feasibility trials (Eldridge et al., 2016), the feasibility hypothesis will be assessed by recruitment and completion rates (see H1), while treatment adherence and adverse events are collected as complementary data.

#### Secondary outcomes

2.9.4

*Drinking behavior* is indicated by change in percentage of days abstinent and percentage of heavy drinking days. These indicators will help describe the preliminary effects of Alc-IT on drinking behavior and will be assessed using the timeline follow-back method (TLFB) at baseline (T1), 1-month (T4) and 3-month follow-up (T5). TLFB (Sobell and Sobell, 1992, 1995) is a procedure to aid recall of past drinking. Providing a relatively accurate estimate of one’s drinking, the TLFB is considered the gold-standard in assessing past drinking behavior. The TLFB will be administered by a telephone interview.

In the EEG sub-study, outcomes include *neurophysiological measures of inhibitory activity*, specifically changes in the N2 and/or P3 components of the event-related potential derived from NoGo trials (see 2.10 for task details and 2.11/2.12 for ERP computation). Additionally, the number of completed sessions, baseline neurophysiological parameters, impulsivity, or performance levels during training will be exploratorily assessed as moderators of the neurophysiological effects of Alc-IT. The topography of the P3 component, featured in hypothesis H3, is the main parameter of interest, while amplitude of the P3 component, as well as topography and amplitude of N2 will be assessed exploratorily.

#### Additional outcomes

2.9.5

*Usability, user experience, and acceptability* will be additionally monitored to support the interpretation of the feasibility outcome (see objective 1): User Experience Questionnaire (UEQ; Schrepp, 2015); this 26-item self-report scale evaluates the user experience of interactive products on a 7-point Likert scale. System Usability Scale (SUS; Brooke, 2013); this 10-item self-report scale evaluates the usability of systems on a 5-point Likert scale. SUS is widely used to assess a broad range of technologies, offering a quick and reliable measure of perceived usability. Facets of Website Content Questionnaire (web-CLIC; Thielsch and Hirschfeld, 2019); this 12-item self-report measure originally evaluates the user experience and content of websites and will be tailored specifically for our app. Open-text and multiple-choice questions concerning drawbacks and strength of the app, technical problems encountered, suggestions for amelioration, intention to continue using the app, and place of using the app will complement this assessment.

#### AUD, psychopathology, and related measures

2.9.6

Alcohol use is additionally assessed using eight adapted items from the Health and Daily Living Form (HDL, Moos et al., 1990), which has been validated in Swiss clinical samples (Moggi et al., 2010, 2007). Participants are also asked to indicate their personal drinking goals (e.g., total abstinence, controlled drinking, Moggi et al., 2010; Moggi et al., 2007), as these may change during treatment and in turn influence the post-treatment drinking outcome (Meyer et al., 2014). Alcohol craving is measured using the German version of the Obsessive-Compulsive Drinking Scale (OCDS-G, Mann and Ackermann, 2000). Additionally, three items rated on a Likert-scale assess the mean and maximum intensity and the frequency of craving over the past seven days (Moggi et al., 2007, 2010). Motivation to change is captured using the German version of the “Taking Steps” subscale from the SOCRATES (Miller and Tonnigan, 1996; Wetterling and Veltrup, 1997), alongside three items derived from motivational interviewing (Demmel, 2005; Miller and Rollnick, 2015), and a single item assessing self-efficacy regarding future alcohol reduction (Ludwig et al., 2013), which are rated on a Likert scale. Psychopathological symptoms are assessed with the 53-item Brief Symptom Checklist, German version (BSCL, Derogatis, 1993; Franke, 2000), yielding scores across nine symptom dimensions and three global indices. Subjective quality of life is measured using the Quality of Life-questionnaire (WHOQOL-BREF, Angermeyer et al., 2000). Emotion regulation is assessed with the 36-item Difficulties in Emotion Regulation Scale (DERS, Gratz and Roemer, 2004). The trait “impulsivity” will be assessed with the Skala Impulsives-Verhalten-8 (I-8, Kovaleva et al., 2012), a validated German short questionnaire to determine the multidimensional construct “impulsivity.” The German version of the ADHD Self Report Scale (ASRS-V1.1, Kessler et al., 2005; Lauth and Minsel, 2014) will be used to screen for ADHD related symptoms. In the EEG sub-study, the 20 items from the BIS (Behavioral Inhibition System) / BAS (Behavioral Approach System) questionnaire will additionally assess behavioral inhibition or approach tendencies (Carver and White, 1994). As in the big C-SURF cohort-study, we will use a slightly adapted version from the validated German version (Strobel et al., 2001).

### Go/NoGo task

2.10

Inhibitory functions will be assessed experimentally with a cued Go-NoGo task (Batschelet et al., 2021; Stein et al., 2018) administered during EEG measurement on a computer in the EEG lab. During the task, alcohol-related and neutral pictures are presented in pseudorandomized order at a 1 Hz rate. Each picture is presented for 900 ms with the interstimulus interval jittered between 100 and 400 ms. Patients are asked to click as fast as possible whenever a new picture appears on screen (Go-trial), unless the same picture is repeated (NoGo-trial), resulting in both alcohol-related and neutral Go and NoGo-trials. Two pseudorandomized orders are established to ensure that unique sequences are presented at pre- and post-training assessments. Alcohol-related stimulus sets are tailored to the patient’s drink of choice (beer, wine, spirits). Stimulus sets consist of 20 alcohol-related and 20 neutral pictures, which were drawn from a validated and controlled stimulus set (Fey et al., 2017) in a way that ensured that (a) alcohol-related stimulus sets did not differ in arousal, craving, alcohol relatedness, valence, luminance, and visual complexity, and (b) alcohol and neutral stimulus sets did not differ in luminance and visual complexity (all *p*-values in ANOVA-based comparisons > 0.05). Each picture is presented 23 times during the task. With 800 Go trials (400 neutral, 400 alcohol-related) and 120 NoGo-trials (60 neutral, 60 alcohol-related), the task operates with Go-NoGo-ratio of 6.67, comprising of a total of 920 trials and lasts approximately 18 min. Given the different picture types (alcohol, neutral) and assessment time points (pre-, post-training), this task allows to compare error rates, reaction times and event-related potentials between picture types, time points and training groups and thus helps to investigate working mechanism of Alc-IT.

### EEG recording and data reduction

2.11

Multichannel-EEG will be recorded in a sound-proof and electrically shielded chamber with a Nihon-Kohden Neurofax 1,100 system from 64 scalp electrodes placed according to the extended 10/20-system. All channels are online referenced against the mean of C3 and C4 and digitally sampled at 500 Hz. Electrode impedances will be kept below 20 kΩ, which is within the recommended range for active electrodes (Brain Products GmbH, 2022). On-line filters will be set at 0.016 Hz (high pass) and 150 Hz (low pass). Off-line, data will be preprocessed using BrainVision Analyzer (Version 2.0, Brain Products GmbH, Gilching, Germany). Preprocessing will include artifact correction via independent component analysis (to remove eye-movement and electrocardiac artifacts) and visual inspection (for remaining artifacts), interpolation of noisy channels, re-referencing to average reference and band-pass filtering. For the computation of event-related potentials (ERPs), clean data will be segmented into epochs from 500 ms before to 1,500 ms after stimulus onset. Individual ERPs will be computed separately for each picture type (alcohol, neutral), response type (Go, NoGo), and time point (pre- and post-training). To isolate inhibitory processes, difference waveforms (dERPs; NoGo minus Go) will be calculated for each condition.

### Statistical analysis

2.12

#### Objective 1 – feasibility of Alc-IT

2.12.1

Following the CONSORT guidelines’ extensions for pilot and feasibility trials (Eldridge et al., 2016), feasibility outcomes will be assessed primarily using data on recruitment and completion rates (indicating attrition), and additionally with treatment adherence, and adverse events. For these indicators, the parameters recommended in the CONSORT guidelines (such as means, data distributions, and percentages as well as narrative descriptions) will be reported. Failure to meet the above-defined indicators for promising feasibility will indicate that H1 cannot be confirmed. No inferential statistical testing will be performed for feasibility outcomes.

#### Objective 2 – preliminary findings regarding the effectiveness of Alc-IT on drinking behavior

2.12.2

The present feasibility RCT is not designed to statistically test hypotheses regarding effectiveness outcomes but will instead provide preliminary data to estimate the effect sizes expected in a future full-scale RCT (Eldridge et al., 2016; Shanyinde et al., 2011; Thabane and Lancaster, 2019). In line with the CONSORT recommendations (Eldridge et al., 2016), preliminary effectiveness will be analyzed descriptively and using effect size indicators. Analyses will follow an intention-to-treat approach. Changes in drinking behavior over time will be analyzed with multilevel mixed-effects models for repeated measures, using baseline measures as the reference for estimating individual change trajectories. The most appropriate model structure, including relevant covariates (e.g., age, treatment setting, baseline severity, nicotine or cannabis use), will be selected based on model fit statistics. Estimated marginal means and standard errors will be reported. Cohen’s d will be calculated as an effect size estimate and presented alongside measures of uncertainty (Eldridge et al., 2016; Thabane et al., 2010). Sensitivity analyses stratified by setting and treatment received will complement the main analyses.

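### The Objective 2 model and covariates are left to unnamed fit statistics on the outcome data, and the stratification factors are not committed to the model

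*Protocol article*

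**What the plan says.** Section 2.12.2 of the protocol article plans multilevel mixed-effects models for repeated measures, "using baseline measures as the reference for estimating individual change trajectories". It then says that the model structure, "including relevant covariates (e.g., age, treatment setting, baseline severity, nicotine or cannabis use), will be selected based on model fit statistics". It does not say which fit statistic will be used, and the bracketed covariates are examples only.

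Section 2.4 allocates patients "using a randomization list stratified by age, gender, and treatment center". Age and treatment setting reappear in 2.12.2 as candidates. Gender does not.

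The same section describes the trial as "not designed to statistically test hypotheses regarding effectiveness outcomes but will instead provide preliminary data to estimate the effect sizes" expected in a full-scale trial. On reporting it says: "Cohen’s d will be calculated as an effect size estimate and presented alongside measures of uncertainty". Section 2.9.4 places the drinking assessments at T1, T4 and T5. Section 2.5 gives the expected data: "we expect to collect complete data for drinking behavior outcome from 90 patients, which aligns with these recommendations".

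**The concern.** Objective 2 tests no hypothesis. Its product is an effect size with its uncertainty, for use in planning the next trial. Three features weaken that product.

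- **Analyst freedom.** With an open covariate list, an open structure and no named criterion, two careful analysts could follow the text and report different values of d. A standard error from the retained model also ignores the fact that the model was chosen on the same data.
- **Design not reflected.** Factors used to balance the allocation belong in the model because of the design, whatever their fit. Here two are optional and one is unlisted.
- **Role of baseline.** Using baseline as the reference for change can mean a model that estimates a difference in change scores. That would give up precision available from data the trial collects anyway.

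This is not a detail left to a separate analysis plan. The article states fit-based selection as the rule, so a plan that fixed the model would contradict it.

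**Working it through.** **The plan's own figure.** The 90 complete patients are a recruitment expectation with no effect size, SD or power attached, so no formula reproduces them. The only possible check is 90/2 = 45 per arm (1:1 assumed; the ratio is not stated). This lies within the cited range: "for small effects, sample sizes ranging from 25 to 75 per study arm are sufficient".

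**Scale of the sampling error.** The half-width of a 95% CI for d is 1.96 × sqrt(2/n + d²/(4n)), with n per arm. At d = 0.2 and n = 45: 1.96 × sqrt(0.04444 + 0.00022) = 0.41. It is 0.56 at n = 25 and 0.32 at n = 75.

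**Covariate selection by fit.** The simulation used 1,500 trials per scenario, N = 90, a true effect of zero, and allocation stratified by age, gender and five centers. The outcome was change at a single follow-up, and all 128 subsets of seven candidate covariates were fitted. Assumed: baseline-to-follow-up correlation of 0.3 or 0.6, and weak or moderate prognostic strength of the strata. Ranges over the four scenarios:

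| Model | True SD of estimate | Mean reported SE | 95% CI coverage |
|---|---|---|---|
| Fixed: baseline, age, gender, center | 0.174–0.204 | 0.170–0.203 | 93.7–94.9% |
| Chosen by AIC | 0.176–0.206 | 0.168–0.203 | 93.6–94.4% |
| Chosen by BIC | 0.174–0.207 | 0.171–0.209 | 94.1–95.1% |
| No covariates | 0.191–0.251 | 0.189–0.255 | 94.7–96.0% |

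For the first three rows, bias was at most 0.002. True precision differed from the fixed model by about 0 to 3%. AIC understated the SE by about 1.5 to 4.5%, against up to about 3% for the fixed model. The Monte Carlo error of a coverage figure is sqrt(0.95 × 0.05/1500) = 0.6 points, so the coverage differences are barely resolved.

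As an outer bound on analyst freedom, always reporting the most favorable of the 128 models gave a bias of 0.07 to 0.11 (residual SD near 1).

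**Structure selection (not simulated).** Suppose a random-intercept structure is kept with equal variances and complete data. It applies the average correlation r̄ = (2r₁ + r₂)/3 to every pair of visits, where r₁ is the baseline-to-follow-up correlation and r₂ the T4–T5 correlation. The reported SE of the change contrast is then sqrt((1 − r̄)/(1 − r₁)) times the true one. Assumed values:

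- r₁ = 0.5, r₂ = 0.6: sqrt(0.467/0.5) = 0.97
- r₁ = 0.3, r₂ = 0.6: sqrt(0.6/0.7) = 0.93
- r₁ = 0.5, r₂ = 0.8: sqrt(0.4/0.5) = 0.89
- r₁ = 0.3, r₂ = 0.8: sqrt(0.533/0.7) = 0.87

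The SE would be 3 to 13% too small. An unstructured covariance removes this.

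**Role of baseline.** Let T1 be one of the repeated outcomes, with a separate mean for each group and visit. With complete data, the group-by-visit contrast is the raw difference in mean change. A baseline covariate entered as a main effect shifts all visits of a patient equally and cancels. In a test fit (90 patients, three visits, random intercept), the contrast equalled the raw change difference (−0.0633). Adding baseline severity left both the contrast and its SE (0.192) unchanged.

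For one follow-up and equal variances, Var(change)/Var(baseline-adjusted) = 2(1 − ρ)/(1 − ρ²) = 2/(1 + ρ):

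| Assumed ρ | Variance ratio | Relative CI width if adjusted, sqrt((1 + ρ)/2) | Change-score sample equal to 90 adjusted |
|---|---|---|---|
| 0.3 | 1.54 | 0.81 | 138 |
| 0.5 | 1.33 | 0.87 | 120 |
| 0.7 | 1.18 | 0.92 | 106 |

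**The case against.** The strongest reply is that little depends on this model. Feasibility is the primary objective, Objective 2 is labelled preliminary, and no test or decision rule uses the estimate. With a CI half-width near 0.41, an SE that is a few percent too small is minor. Setting is a named candidate, and sensitivity analyses stratified by setting are planned. This stands as an argument about severity. It does not remove the point, because the estimate and its interval are what Objective 2 delivers.

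A reader might infer that fit-based selection makes the estimate imprecise and untrustworthy. The simulation does not support that: with randomized arms, AIC or BIC selection of covariates gave no material bias and coverage close to that of the fixed model. Nor does the article suggest that the most favorable model would be reported. It selects on fit, so the 0.07 to 0.11 bounds what the wording leaves open and does not predict what will happen.

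A reader might also take the variance ratios as the cost of fit selection, or as a certain loss. They are neither. They compare a change score with baseline adjustment, and they apply only on one natural reading of the text. A model with a common baseline mean fits the same words and has no such loss. In a single-endpoint change model with baseline as a candidate, fit would almost always retain it: its correlation with change is −sqrt((1 − ρ)/2), or −0.59 at ρ = 0.3 and −0.50 at ρ = 0.5. That argument does not carry over to a model with T1 among the outcomes, where the covariate main effect cancels.

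Finally, a ban on all model checking would go too far for percentages bounded at 0 and 100. That is accepted in the remedy.

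**Conclusion.** The point holds at moderate severity. Section 2.12.2 makes the structure and covariates depend on the outcome data through an unnamed criterion and an open list, and it does not commit the stratification factors of section 2.4 to the model. The consequence is analyst freedom in the reported d and a somewhat understated standard error. The part due to AIC or BIC covariate selection is immaterial. The part due to choice of covariance structure rests on assumed correlations and was worked out by formula only. Missing data were not examined.

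The precision issue is separate and conditional. It requires unconstrained group means at T1. Its size depends on a baseline-to-follow-up correlation that the article does not give, and the formula is for one follow-up with complete data. If a common baseline mean is intended, the article only needs to say so.

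**What to change.** Replace the fit-selection sentence in section 2.12.2 with one primary model, fixed before outcome data are examined:

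- outcome at T4 and T5;
- group, visit and group-by-visit;
- the baseline value of the same outcome (or T1 kept as an outcome with a common baseline mean);
- age, gender and treatment center, as used in the randomization;
- unstructured covariance over visits.

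Report Cohen's d with its 95% CI from this model. Keep baseline nicotine and cannabis use, any fit-selected model, and any alternative distribution for the bounded percentages as labelled secondary analyses, with the fit criterion named.

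The cost is wording plus a few degrees of freedom. With age as one term, gender as two categories and five centers, the stratification factors use 1 + 1 + 4 = 6, and the baseline value one more, out of about 90 patients.
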